### Participation

All first grade students in the DSP schools receive the intervention, as this is an integrated whole school program. Similarly, all students in the MHST schools have the opportunity to come in contact with the MHST if they need it as the MHST are part of the student services.

### Consent procedure

Informed active consent by parents is required for the participation of students below 16 years of age at time of survey data collection. The project administration only has access to student, and not parent contact information. Therefore written information about the study and survey was distributed to students via mail, email and sms with instructions to forward this to their parents. Consent could be given either by SMS to the project coordinator, or via an electronic response form in which parents could respond yes or no. For C1, a total of 820 students needed consent. The total response rate for consent request obtained for this group was 72%, and a total of 70% agreed that their child could participate. For C2, a total of 706 students needed consent. The total response rate for consent request obtained for this group was 81%, and a total of 80% agreed that their child could participate.

### Baseline assessment and follow up

Each student cohort will be assessed through survey on three (C1) or two (C2) occasions (Figs. 2 and 3):Baseline: during the first or second week of school in the first semester of grade 1C1: August 2016 (already completed)C2: August 2017 (already completed)First follow-up: in the second semester of grade 1C1: March 2017 (already completed)C2: March 2018Second follow-up: in the second semester of grade 2C1: March 2018

Registry data on drop-out, absence and school grades after grade 1, 2 and 3 will be linked to survey data. In addition, survey data from grade 1 teachers of the C2 will be collected in August 2017 and March 2018, to assess any change in teacher perceptions on their relational competence over the intervention period. However these data will be considered supplemental and not part of the quantitative effect evaluation.

### Intervention

Schools in the intervention groups (I1 and I2) started the planning of intervention implementation in the spring of 2016, and C1 students in the intervention schools received the interventions immediately after semester start in August 2016. The same procedure will be followed for the C2 students, starting upper secondary school in August 2017. Schools in the control group will be offered the DSP after completion of the second intervention year, starting in August 2018.

#### The Dream School Program (DSP)

The DSP is developed by the Norwegian NGO *Adults for Children* (AfC) [30]. The program is a whole school program, involving staff and students, with the aim of creating learning environments where students are confident and experience a sense of belonging, and where mental health is promoted [30]. A core aspect of the DSP is the training of peer leaders from grade 2 or 3, so called student mentors, as important executers of the program. The DSP involves specific core elements that must be carried out in order for it to be properly implemented. These are the Dream Class 1 and 2, and the Dream Class poster which involves making guidelines for a good psychosocial class environment. The student mentors are to be actively involved in collaboration with class teachers in carrying out these core elements. In addition, they welcome the new students on the first day of school, carry out theme gatherings, and are intended to be actively involved in creating meeting points for socialization. In addition, the school is encouraged to incorporate other activities that they usually carry out as part of a more systematic work for improving the psychosocial environment at the school. The effectiveness of the DSP has previously been evaluated in two pilot studies with promising effects on academic self-efficacy, teacher support, and intention to continue upper secondary school the following year [31, 32].

#### The Mental Health Support Team intervention (MHST)

The MHST intervention is developed in a collaboration between employees at Bodin upper secondary school in Norway [27] and researchers at Nordland Research Institute (NRI) [33].

MHST is also a whole school project but aimed at specific students at risk of dropping out. It is a systematisation of the student services throughCo-location of services and staff working in services“One open door” to increase accessibility to the services and staff for studentsFocus on the transition from lower to upper secondary schoolClose follow-up of students at risk to ensure tailored help to each studentEarly intervention and follow up when student starts being absent from school

This work demands cross- and multidisciplinary collaborations within the MHST, between MHST and school leadership, and between lower and upper secondary schools.

### Intervention delivery

#### DSP

The delivery of the DSP involved giving information to all DSP school leaders. Next, a resource group, comprised of five to seven representatives from the school leadership, student council and teachers were established and trained over two days each in workshops held by AfC. The resource groups in turn had responsibility for recruiting student mentors which were trained in student mentor gatherings by AfC staff. Student mentors were trained in workshops in the spring of 2016 for C1 and 2017 for C2. In May, June and August, of 2016 and 2017, workshops with school staff were carried out to prepare the schools for the school year with Dream school implementation. During the year, student mentor and resource group gatherings were organized separately for exchange of experience and inspiration between DSP schools. In addition, representatives from AfC visited a selection of the schools during the fall of 2016, and had phone conversations with all DSP schools in August 2016 and June 2017, in addition to email contact throughout the school year. They will follow the same procedure in the school year of 2017/2018.

#### MHST

The delivery of the MHST involved a different approach than the DSP as it is more of a structural intervention. Seminars with school leaders and team members were held in June and August 2016 to inform about the structure and core elements of MHST, and to discuss local solutions for implementation. Specifically, many schools had to undergo a reorganizing to ensure co-localization and “one open door”. Schools also vary in the employee situation with respect to number and type of workers associated with student services. Hence, establishing the team of 3-5 persons was one key priority in the early implementation phase. Schools with MHST have close follow-up with representatives from Bodin and with county coordinators (see more details on this under the section on Implementation quality and intervention fidelity below).

### Implementation quality and intervention fidelity

To ensure motivation and implementation quality, a range of dialogue meetings between project partners were held before and after recruitment of schools. Meetings between the project and county leaderships, and the intervention implementers (AfC and Bodin) were held before and after recruitment, and regular meetings are planned throughout the project period. Information meetings were held with school leadership teams, teachers and student representatives after recruitment.

To ensure intervention fidelity, yearly gatherings have been organised and will be organised throughout the project period separately for the peer mentors, the resource group members of each DSP school, and members of MHST to share experiences and motivate each other. In each gathering, each MHST is required to develop an action plan for their specific work the coming academic year. Similar gatherings are also organized at the county level with the county project coordinator involved. In the MHST gathering in June 2017, a representative from the leadership in each school with MHST was also present to secure understanding for the MHST work at the leadership level of the school. In addition, representatives from Bodin have phone calls with each team every other week to discuss progress, challenges and solutions.

### Measures

The primary outcomes in COMPLETE are increased completion of, and presence at upper secondary school, academic achievement, and mental health and well-being (Table 3). Data on the three former are obtained for each student participating in the study from county registries, and linked with survey data. More specifically, data on the completion of the first, second and third grade of upper secondary school; days and hours of time absent from school in the first, second and third grade of upper secondary school; and average grade obtained by each student after the first, second and third grade of upper secondary school will be collected from registries. To classify a student as dropout, the student must have quit school, and not just switched schools or study programs.

**Table 3 Tab3:** Outcome measures

	Measure/definition	Source of measure	Data source
Primary outcomes			
Dropout/Completion	Drop-out is indicated if the student has a) not completed upper secondary school within five years after enrolment in upper secondary school, or b) if the student quit school and is without any regular activity during the course of the study period, i.e. grade 1-3 of upper secondary school. Completion of school year is indicated if the student has passed all subjects at the end of the current school year	Registry data	County registry data
Presence/Absence	Average days and average hours absent the past school year	Registry data	County registry data
Academic achievement	Average grade at closure of each school year in project period	Registry data	County registry data
Mental health	Short form of Symptom Check List (SCL-5)	Tambs et al., 1993 [34]	C1 and C2 Student survey
Mental wellbeing	Warwick-Edinburgh Mental Wellbeing Scale (WEMWBS)	Clarke et al., 2011 [35]	C2 Student survey
Secondary outcomes			
School satisfaction	Multidimensional Student’s Life Satisfaction Scale: Three items from the school satisfaction dimension	Huebner, 1994 [37]	C1 and C2 student survey
Loneliness	Loneliness Scale	Mittelmark et al., 2004 [39]; Kraft & Loeb, 1997 [38]	C1 and C2 student survey
Mediators			
Relatedness	Wichstrøm Social Competence Scale	Wichstrøm, 1995 [41]	C1 and C2 student survey
	Teacher and Classmate Support Scale	Torsheim et al., 2000 [44]	C1 and C2 student survey
	Positive Youth Development Connection Scale	Geldhof et al., 2014 [43]; Lerner et al., 2005	C1 and C2 student survey
	How many close female friends do you currently have?	Single item	C1 and C2 student survey
	How many close male friends do you currently have?	Single item	C1 and C2 student survey
Autonomy	Ten items from the Learning Climate Scale	Black & Deci, 2000 [45]	C1 and C2 student survey
Competence	How do you think you will perform academically this school year?	Single item	C1 and C2 student survey
	Academic Self-Efficacy Scale	Roeser et al., 1996 [46]	C1 and C2 student survey
Class climate	Caring Climate Scale (CCS)	Newton et al., 2007 [47]	C1 and C2 student survey

Data on mental health and wellbeing are obtained through surveys based on validated measures. Specifically mental health is measured by the short form of the Symptom Check List (SCL-5) [34], and mental wellbeing is measured by the Warwick-Edinburgh Mental Wellbeing Scale (WEMWBS), previously validated for use in adolescent populations in the UK [35], and in the Norwegian setting in an adult primary health care patient population [36].

Secondary outcomes in the trial include school satisfaction, measured through three items from the school dimension of the Multidimensional Students’ Life Satisfaction Scale [37] and loneliness [38–40] (Table 3). These data are also obtained for each student through surveys and validated measures.

Mediators in the trial include measures of psychosocial aspects, specifically measures of experienced relatedness [41–44], teacher autonomy support [45], competence [46], and climate [47] in the school, class and other contexts of the youth. These data are obtained for each student through surveys and validated measures. See Table 3 for details on the measures.

Moderators or background variables include student gender (male/female/other), ethnicity, socioeconomic status (student reported parental education level and family economic standing), and student line of schooling (generalised or vocational).

In addition, data on several other indicators relevant to youth social and emotional life are collected through the surveys. However, in this study protocol, only the most relevant indicators to the COMPLETE study aims are described.

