**Methods/Design:**

The COMPLETE RCT is aimed at youth in upper secondary school, grade 1 (age 15-16 years), and examines the effect of the combination of the DSP and the MHST; and the DSP only, compared with a comparison group on the following primary outcomes: student completion, presence, average grade, and self-reported mental health. Seventeen upper secondary schools from four counties in Norway were randomized to one of the three arms: 1) DSP and MHST; 2) DSP; and 3) comparison (offered DSP intervention in 2018/2019). The study will evaluate the interventions based on information from two cohorts of students (cohort 1 (C1) and cohort 2 (C2)). For C1, data was collected at baseline (August 2016), and at first follow-up seven months later. Second follow-up will be collected 19 months after baseline. For C2, data was collected at baseline (August 2017), and first and second follow-up will be collected similarly to that of C2 seven and 19 months respectively after baseline. Process evaluations based on focus groups, interviews and observation will be conducted twice (first completed spring 2017).

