## Methods

### Study design

COMPLETE is an ongoing school-based three-armed cluster RCT in upper secondary schools in four counties in Norway. The trial started in August 2016, and will end in June 2019. It follows two cohorts of students from when they start upper secondary school and until they graduate (C1) or until completion of second grade (C2). The study is non-blinded, and the design includes two intervention groups and a control group. Tables 1 and 2 outline the project data collection and intervention timeline.

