### Recruitment of schools

Recruitment of schools started in November 2015 with information meetings and written invitations. All upper secondary schools in the four counties were invited to report their interest in participation in the trial. Eligibility criteria were not having been or currently being involved in the DSP or the MHST *or* in similar programs, *or* in other similar research projects. An invitation letter was sent to all schools in the counties via the county administration describing study aims, and project participation. The recruitment process lasted until February 2016. A total of 19 schools reported interest in joining the project, of which 17 schools met the eligibility criteria. These schools comprised approximately 3100 grade 1 students in total. All students are eligible for participation in the DSP and MHST, but for the effect evaluation and survey data collections, students with special needs and students in so called introductory programs (i.e. students with very limited or no knowledge of Norwegian language) were excluded. The final student N is based on students registered at each of the schools the final days before survey data collections. However, it should be noted that due to a high degree of natural fluctuation between schools and study programs the first week of each school year, it is expected that the study N from registries will deviate quite a bit from the survey sample. For C1 the N was 3003 grade 1 students and for C2 the N was 3022 grade 1 students. In C2, approximately 200 class teachers will also receive a survey.

Figure 2 presents the flow chart of participation through the COMPLETE trial per now.

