### Randomization of schools

Representatives from Oxford Research who had no prior knowledge of the recruited schools allocated schools to the intervention or control groups according to a computer generated randomization list. To ensure an equal balance of intervention and control groups in each county, stratified randomization was practices in which schools were stratified by county. All schools were given a random number ranging from 0 to 1 by using a randomisation command in the statistics software of Stata 14. Stata generated a random number based on a chosen key. Next, the schools were sorted after the size of the random number in each stratum. The school with the highest number was appointed to the intervention group 1 – I1 (DSP only), the school with the second to highest number was appointed to intervention group 2 – I2 (DSP and MHTS), and the school with the third to highest number was appointed to the control group – C. This procedure was repeated until all schools in each stratum were appointed to a group.

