#### Process evaluation

The process evaluation builds on two rounds of qualitative interview studies and school visits in 12 schools (the COMPLETE intervention schools) encompassing 19 subdivisions. The studies are conducted in the spring of 2017 (completed) and of 2018. They encompass qualitative interviews, both individual and group interviews, with school leadership (headmaster), subdivision leaders (e.g. study program leaders), class teachers, resource groups for the DSP, student mentors (DSP), students in the DSP, the MHST (counsellors, school nurses, team coordinators) and students in the target group for MHST. Every study (both 2017 and 2018) encompasses approximately 120 interviews and includes around 300 different persons. Every interview has a duration of approximately one hour. Every school visit covers three days and includes both interviews and observation of common areas like the canteen, social zones, outdoor areas, administration area and the teacher common room. Specific interview guides are developed for the different target groups in the study. These are structured interview guides with follow-up questions. The aim of the interviews is to capture the experiences the schools have with the implementation of the two interventions.

All data are stored according to guidelines and requirements for safe storage of data in the University of Bergen storage, SAFE.

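### The effect analysis names clustering as its only adjustment; adding county and the intake variables already collected would be a nearly free improvement, most of all for completion, absence and grades

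*Protocol article*

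**What the plan says.** All locations are in the Protocol article.

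- **Allocation.** The abstract states "Seventeen upper secondary schools from four counties in Norway were randomized to one of the three arms". Under Randomization of schools, "stratified randomization was practices in which schools were stratified by county"; no other stratum is named. Process evaluation describes "school visits in 12 schools (the COMPLETE intervention schools"), which leaves 5 control schools.
- **Timing.** Under Recruitment of schools, "The recruitment process lasted until February 2016". Under Intervention, the intervention schools "started the planning of intervention implementation in the spring of 2016". C1 entered in August 2016. For the second cohort, "The same procedure will be followed for the C2 students, starting upper secondary school in August 2017".
- **Entry to the analysis set.** Recruitment of schools bases the student N on those registered at each school in the last days before the survey. It expects considerable movement between schools and programmes in the first week. Study design adds: "The study is non-blinded".
- **Intake variables.** Measures says "Moderators or background variables include student gender (male/female/other), ethnicity, socioeconomic status", and the same sentence goes on to line of schooling (general or vocational).
- **Analysis.** Statistical analyses adjusts the intention-to-treat analysis for clustering and names no covariate. Gender, socioeconomic status and ethnicity appear there as potential moderators, to be described by arm. Moderation is assessed in growth models and subgroups in secondary analyses. Line of schooling is absent from the section.
- **Outcomes.** Completion, absence and grades come from registries after grades 1, 2 and 3. The SCL-5, school satisfaction, loneliness and (C2) WEMWBS come from surveys with a baseline in the first or second week of grade 1.

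**The concern.** Randomising schools balances, in expectation, what the schools were at allocation. It does not by itself fix which students enrol later in an unblinded trial. In the combined arm, the support team's work includes the transition from lower secondary school and students at risk of dropping out, so a route to different intakes is conceivable, especially for C2. Separately, with 5 to 7 schools per arm and only county as a stratum, the mix of general and vocational students can differ between arms by chance.

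The survey outcomes have a starting value in a growth model, which takes up much of an initial difference. That baseline is taken in weeks 1 to 2, when intervention contact has already begun, so it is not strictly pre-intervention. Completion, absence and grades, which are three of the four primary outcomes listed in the abstract, have no starting value at all. For these, a clustering-only model leaves explainable between-school variation in the error and has nothing to offset a measured intake difference.

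**Working it through.** **1. Timing.** The randomisation date is not given. Recruitment ended in February 2016 and intervention schools were planning in spring 2016, so allocation was evidently known by then. Even if spring is taken to run to June 2016, C1 entry in August 2016 is later, and C2 entry in August 2017 is 14 months later.

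**2. Schools per arm.** Within a county, schools are dealt in the order DSP only, DSP plus MHST, control. A county with h schools therefore supplies the whole-number part of h/3 as controls. Five controls account for 15 of the 17 schools in complete triplets, which leaves 2. If both are in one county, the split is 6/6/5; if they are in two counties, it is 7/5/5. No other split fits 12 intervention schools.

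**3. The plan's benchmark.** The sample-size paragraph targets d = 0.25. Per arm, 2 × (1.960 + 0.842)² / 0.25² = 251.2, so 252. The design effect is 1 + 19 × 0.05 = 1.95. The total for two arms is 2 × 252 × 1.95 = 983 students, or 983/20 = 49.1 classes, against the stated 975 and 49. This reproduces and is not in dispute; it only supplies the 0.25 used for scale below.

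**4. Chance imbalance in line of schooling.** Two inputs are assumptions, not in the documents: the between-school SD of the vocational share (s = 0.2 to 0.4) and the difference in completion between lines (5 to 20 percentage points).

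SD of the arm difference in vocational share = s × √(1/6 + 1/5) = s × 0.606. The shift in the completion contrast for a one-SD imbalance is that figure times the gap:

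| s | SD of arm difference | Gap 5 | Gap 10 | Gap 15 | Gap 20 |
|---|---|---|---|---|---|
| 0.2 | 0.121 | 0.6 | 1.2 | 1.8 | 2.4 |
| 0.3 | 0.182 | 0.9 | 1.8 | 2.7 | 3.6 |
| 0.4 | 0.242 | 1.2 | 2.4 | 3.6 | 4.8 |

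Shifts are in percentage points. On a normal approximation, the probability that two arms differ by more than 10 points in vocational share is 41%, 58% and 68% for the three values of s.

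**5. Sensitivity to the split.** Under 7/5/5 the multiplier is √(1/7 + 1/5) = 0.586 or √(1/5 + 1/5) = 0.632. The range becomes 0.6 to 4.7 or 0.6 to 5.1 points, so the picture does not depend on which split occurred.

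**6. On the standardised scale.** If lines differ by 0.3 to 0.5 SD on an outcome (assumed), the one-SD shift runs from 0.3 × 0.121 = 0.04 to 0.5 × 0.242 = 0.12, against the target of 0.25.

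**7. What is not sized.** Steps 4 to 6 cover chance imbalance only. Nothing in the document allows selective enrolment to be quantified.

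**The case against.** The strongest reply is that this is a condensed article and the analysis plan is not shown. A covariate list is commonly left to that plan, and nothing in Statistical analyses rules adjustment out. That stands, so the point is put as an improvement and not as an error. It still goes further than a missing detail, because the section does say what the effect analysis is adjusted for and gives the variables it mentions other uses.

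Three stronger readings are tempting, and the document supports none of them.

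- A reader might infer that the intake variables are reserved for moderation. Measures also calls them background variables, and Statistical analyses plans to describe gender, socioeconomic status and ethnicity by arm, so part of the transparency sought is already there.
- A reader might infer that the arms did recruit different students. No passage says so. The early movement between schools is described as natural, and the transition work is described as support for students, not as recruitment.
- A reader might infer that chance imbalance biases the effect. It does not. Under randomisation it is sampling error, and an analysis that handles clustering correctly at the level of the randomised school carries it in the standard error.

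Two limits on the remedy also stand. Line of schooling recorded at the survey may already reflect first-week switching. Covariates also cannot remove selection on unmeasured traits such as motivation.

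**Conclusion.** The point holds as a low-cost improvement. The stated effect analysis, adjusted for clustering only, leaves unused the stratification factor and prognostic variables already in hand. The case is clearest for completion, absence and grades and weaker for the survey outcomes.

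The illustrative size is 0.6 to 4.8 percentage points on the completion contrast for a one-SD chance imbalance, with 6 versus 5 schools. This rests entirely on the assumed between-school SD and the assumed gap between lines. It measures precision that could be recovered, not bias. Differential intake after allocation remains a risk that reporting would expose and adjustment would partly offset. The sample size does not change.

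**What to change.** State that the main effect models, above all those for completion, absence and grades, include as fixed covariates:

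- county, as the randomisation stratum;
- line of schooling at entry, taken from registry records where available;
- gender, ethnicity, and parental education/family economy.

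Handle missing covariates with the multiple imputation or FIML already planned. Report these intake variables by arm separately for C1 and C2, and give cohort-specific effect estimates beside the pooled one, so that a shift in the C2 intake would be visible. Say plainly that adjustment removes only measured differences.

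The cost is wording, plus confirmation that line of schooling at entry can be retrieved. County uses 3 school-level degrees of freedom: with 17 schools, 17 − 1 − 2 (arms) − 3 (county) = 11 remain. The statement should be dated. Trial status reports one of five registry linkages complete by 1 November 2017, and covariates chosen after outcomes are in hand are open to challenge in a non-blinded trial.
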